### Participant timeline

The data for the primary outcome will be measured after the GP appointment (*t*_*1*_^*GP*^) with a self-complete paper survey (control arm) and collected in the NeTKoH database by the tele-neurologist (intervention arm) at *t*^*T*^. At baseline (*t*_*0*_^*GP*^), organizational and demographic data of the settings and GPs will be collected with a survey by the study center.

Secondary outcome data (see Table 1) regarding the enrolled patient’s quality of life and health status will be assessed for both groups after the GP appointment regarding a neurologic problem (*t*_*0*_^*P*^) with the self-complete EQ-5D-5L. In order to minimize interference in the GP offices’ everyday routine, only this time point (*t*_*0*_^*P*^) was deemed feasible. Patients’ demographics will also be collected in a self-complete paper survey. Their disease characteristics will be documented by the GPs at *t*_*1*_^*GP*^ in the GP survey. The subsequent treatment (referrals) of patients and further process-related data will be documented by the tele-neurologist in the NeTKoH-database at *t*^*T*^. Just-in-time care endpoints, such as time until a neurologist appointment, and specialty diagnostics, as well as the number of hospital stays, will be assessed at *t*_*1*_^*P*^ for both groups taken in the form of a standardized telephone interview 3 months after the patients’ initial GP appointment. All patient answers to the standardized questions at the 3-month follow-up (*t*_*1*_^*P*^) will be electronically documented by the study team. The patients’ length of stay (LOS) at the hospital between *t*_*0*_^*P*^ and *t*_*1*_^*P*^ will be collected via claims data provided by the two participating health insurance providers.

**Table 1 Tab1:** NeTKoH—secondary outcomes, timepoints^a^, and instruments

Outcome	Timepoint	Measurement instrument
Subsequent treatment (referrals): GP/neurologist/other medical specialist/inpatient care/others *(intervention group – control group)*	*t*_*1*_^*GP*^*, t*^*T*^	Questionnaires GPs, NeTKoH-database
Time until appointment neurologist (days) *(intervention group – control group)*	*t*^*T*^ *t*_*1*_^*P*^	*Intervention group*: NeTKoH-database *Control group*: standardized phone interview
Time until appointment for indicated initial specialty diagnostics: a) cMRT, cCT b) electrophysiology of nerves/muscles, c) ultrasound of brain supplying vessels, d) Electroencephalography *(intervention group – control group)*	*t*_*1*_^*P*^	Standardized phone interview
Number of hospital stays (for *t*_*0*_^*P*^*- t*_*1*_^*P*^) *(intervention group – control group)*	*t*_*1*_^*P*^	Standardized phone interview
Number of hospital days/length of stay (for *t*_*0*_^*P*^*- t*_*1*_^*P*^) *(intervention group – control group)*	*t*_*1*_^*P*^	Claims data
Quality of life *(intervention group – control group)*	*t*_*0*_^*P*^*, t*_*1*_^*P*^	EQ-5D-5L (hybrid): self-complete paper (*t*_*0*_^*P*^*)* and standardized phone interview (*t*_*1*_^*P*^)
Health status *(intervention group – control group)*	*t*_*0*_^*P*^_*,*_* t*_*1*_^*P*^	EQ-5D-5L VAS (hybrid): self-complete paper (*t*_*0*_^*P*^*)* and standardized phone interview (*t*_*1*_^*P*^)

*GP* general practitioner, *t*^*T*^ after teleconsultation,* t*_*0*_^*P*^ directly after initial GP appointment (patients), *t*_*1*_^*P*^ after a 3-months follow up (individual for patients), *t*_*1*_^*GP*^ directly after initial GP appointment (GPs), *cMRT* cranial computed magnetic resonance imaging, *cCT* cranial computed tomography, ^a^timepoints assessed, *VAS* visual analog scale

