### Intervention

During the intervention phase of the trial, all clusters will receive neurologic teleconsulting. In order to do so, they will be equipped with a certified telemedical system (VIMED® Praxis) provided by the company MEYTEC (Werneuchen, Germany). This telemedicine device is a face-to-face video-conferencing tool connected with the department of neurology at UMG. It allows for a remote audiovisual interaction between a tele-neurologist located at UMG and the participating GP, together with the patient. The NeTKoH video-conferencing system is a hardware solution with integrated microphones and speakers, as well as a remotely controllable camera. Internet access is achieved via mobile radio.

Eligible patients can be included in the study by the participating GPs after informed consent is given by the patients in the course of their consultation visit. Patients, who are willing to participate in the study, will be asked to wait while a medical assistant of the GP’s office activates the telemedical system in a separate room in order to start the registration process for the consultation electronically. Through the registration, a medical assistant located at the neurology department (UMG), is notified and schedules an appointment. Thereby, a notification appears on the telemedicine device located in the GPs office. The GP’s office will then schedule the consultation and will inform the patient about the planned start of the consultation with the tele-neurologist, which then takes place in the GP’s examination room. The teleconsultation, which is supposed to be limited to a maximum of 15 min, includes questions about symptoms, diagnostics performed, treatments, referrals, medications, and a brief symptom-oriented clinical examination. After the consultation, the findings and recommendations are electronically documented and a print-out in the GP’s office is created.

During the time a cluster is randomized to the control phase, treatment will be provided according to ‘usual care’ after informed consent is given by the patient. This means that clusters delivering the control condition will not be equipped with a telemedicine device, and patients will have no access to a tele-neurologist during their GP visit. Treatment will follow local standards.

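### Time until neurologist appointment: the text uses the 3-month interview in both groups, Table 1 a different source and timepoint in each; reconcile them and define one event

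*Protocol article*

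**What the plan says.** All references are to the protocol article.

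- **Participant timeline, running text.** The care endpoints are described as those "such as time until a neurologist appointment, and specialty diagnostics, as well as the number of hospital stays, will be assessed at" the follow-up timepoint t1P. On arms and mode of collection, the wording is "for both groups taken in the form of a standardized telephone interview 3 months after", counted from the first GP visit. One source and one timepoint therefore serve both groups.
- **Participant timeline, Table 1.** The row "Time until appointment neurologist (days" lists the timepoints tT and t1P and gives the instruments as "Intervention group*: NeTKoH-database *Control group*: standardized phone interview". The table footnote defines tT as "after teleconsultation".
- **Participant timeline, database entries.** Referrals and process data in the intervention group "will be documented by the tele-neurologist in the NeTKoH-database at" tT.
- **Intervention.** Once a patient is registered through the telemedical system, a medical assistant at the neurology department "is notified and schedules an appointment". Control patients have no access to a tele-neurologist.
- **Statistical analysis.** Time until neurologic appointments is secondary outcome 4. It is analysed with a generalized linear mixed effects model at a significance level of 0.05.

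**The concern.** The text and the table give incompatible instructions for one named, tested outcome. Extraction from PDF does not explain this: the arm labels in the table are legible, and the rows for specialty diagnostics and hospital stays, which the same sentence covers, show the interview at t1P with no split by arm.

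Which version is followed matters. Under the text, both groups answer the same question at the same time. Under Table 1, one arm is measured by study staff at the point of treatment and the other by patient report three months later. Fixed time effects and random cluster effects cannot remove a measurement difference that coincides with the intervention. The outcome is one of the patient-level effects named in the Objectives, so a reader would take a difference as evidence about access to neurologic care.

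**Working it through.** **1. The plan's own figure.** The article states no power for this outcome. The nearest figure is the power of 0.80 for patient-reported secondary endpoints (d = 0.20, 310 versus 531 patients, two-sided 0.05). With noncentrality 0.20 / √(1/310 + 1/531) = 0.20 / 0.0715 = 2.80, power is about Φ(2.80 − 1.96) = Φ(0.84) = 0.80. The exact noncentral t value is 0.798. The figure reproduces. It neither supports nor weakens the present point.

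**2. The two statements side by side.**

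| | Running text | Table 1 |
|---|---|---|
| Intervention source | 3-month interview | NeTKoH database |
| Intervention timepoint | t1P | tT |
| Control source | 3-month interview | 3-month interview |
| Control timepoint | t1P | t1P |

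The timepoint cell does not label the arms. The assignment follows from the instrument cell, and tT cannot exist for a control patient.

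**3. What the intervention value could be under Table 1.** The database is completed after the teleconsultation. The only neurologist contact prompted by the GP visit that it can then record as having taken place is the teleconsultation; at most, a planned later date could be noted. A control patient can report only a usual-care appointment. The article defines neither the event nor the database field, so this is the most plausible reading and not a stated fact.

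**4. Fit with the primary outcome.** A problem counts as solved when there is no outpatient or inpatient referral. The teleconsultation cannot count as such a referral, or no patient who received it could be solved. If secondary outcome 4 counts it as the neurologist appointment, the two outcomes treat the same contact in opposite ways. The plan should say so if that is intended.

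**5. Missing data.** The inputs are 555 control and 534 intervention patients, and the 30% dropout stated for patient-reported endpoints. The assumption is that this 30% applies to the interview item.

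- Under Table 1: control 555 × 0.70 = 388.5 with an interview; intervention up to 534, since the database does not depend on the interview. Availability is 70% against up to 100%.
- Under the text: control 388.5; intervention 534 × 0.70 = 373.8. Availability is 70% in both.

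**6. Selection among those seen.** The planning assumptions put the solved proportion at 0.20 in control and 0.30 in intervention. So at most 80% and 70% have any referral from the index visit, to a neurologist or elsewhere. If dropout is unrelated to referral, those interviewed who could report an appointment arising from such a referral number at most 0.80 × 388.5 = 310.8 and 0.70 × 373.8 = 261.7. A mean wait among those seen would therefore compare differently selected patients even with a common source, which is why patients not yet seen must stay in the analysis.

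**The case against.** Table 1 is the more specific statement. It splits only this row by arm, which looks deliberate, and a condensed article may leave the exact event definition to the full protocol or analysis plan. This stands in part: nothing in the article settles which version is right, and an absent definition alone would be no finding. It does not remove the contradiction, which is printed in one section.

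It can also be said that faster contact with a neurologist by video is what the trial sets out to deliver. The Objectives describe specialty care reaching patients in their own GP practice. This stands too. If the teleconsultation is the event, a shorter time is a real access gain. It is, however, largely produced by the intervention itself, and should be labelled as such and not read as a shorter wait for usual specialist care.

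A reader might infer more: that the arms certainly time two different events, and that a large difference is therefore guaranteed even without benefit. The documents do not support that. The event is undefined, no interval between registration and teleconsultation is given, and no usual-care waiting time is stated. If the text is the version in use, the problem of different events largely falls away.

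Restricting the outcome to in-person visits and analysing only those seen would not be a sound remedy. It conditions on referral, which the intervention is expected to change, and leaves no rule for patients never seen.

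**Conclusion.** The plan is wrong as written on secondary outcome 4: the text and Table 1 cannot both be followed. That part is certain.

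If Table 1 is followed, source, timepoint and missingness differ by arm. Most plausibly the timed event differs as well, so a difference could largely reflect trial scheduling and measurement method. This second part is conditional on Table 1 being the version in use and on the database holding the teleconsultation or a planned date. The size of any distortion in days cannot be derived from the article. The only quantity that can be shown is the imbalance in available data, 70% against up to 100%, and it rests on applying the stated 30% dropout to this item.

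The scope is one of seven secondary outcomes; the primary outcome is untouched. The correction should be made before analysis, but it does not threaten the trial.

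**What to change.** 1. Reconcile the running text and Table 1 so that both groups use one event definition, one time zero (the initial GP appointment) and one source (the 3-month interview).
2. State whether the teleconsultation counts as the event.
3. Keep patients without a neurologist appointment by 3 months in the analysis as not yet seen (censored), and do not drop them. A discrete-time model with a complementary log-log link does this and remains a generalized linear mixed model with fixed time and random cluster effects, so the planned model family need not change.
4. If time to first neurologist contact including the teleconsultation is reported, give it its own label as an access measure that is largely produced by the intervention.

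**Cost.** If the interview asks the item in both groups, as the text says, the cost is a correction to Table 1 and a short definition. Intervention patients are already interviewed at t1P for diagnostics, hospital stays and the EQ-5D-5L. The downside is timing: recruitment began in October 2021 and this protocol version dates from June 2023. If the intervention-group interview did not contain the item, the values for patients already followed up are missing. The number affected must then be reported, and the item added for the remaining interviews.

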### Data collection, management, and quality control

Paper surveys for patients and GPs are used to increase the cooperation of GPs and patients during the trial, according to local experts in the study group. However, all paper surveys were created using the software program evasys [21], so that an automatic export of the survey answers at the study center of the participating university hospital (UMG) will be possible for the subsequent evaluation at Charité – Universitätsmedizin Berlin (Charité). The patient and GP paper surveys will be picked up once a month from the GP offices by UMG study personnel.

The standardized telephone interview at 3-month follow-up for patients will be based on a survey, pre-programmed in an evasys web surface, which will be filled out by the interviewer during the call. Since we are expecting attrition to occur, especially at the 3-months follow-up, reasons for dropouts and loss-to-follow-up will be collected.

The NeTKoH-database was programmed using automatic plausibility checks and mandatory fields for data entry. Technical training of the GP offices regarding the use of the teleconsulting system will take place prior to the start of the intervention. On-site monitoring, a feedback loop, and measures to inquire regarding implausible or missing data by the study personnel will be instituted. The study personnel will receive training for the documentation in the NeTKoH database and the evasys web surface. All surveys were piloted before the start of the intervention.

All data collection, handling, transferring, processing and storage will follow the project’s comprehensive data protection concept approved by the responsible data protection officers. The primary and secondary data of NeTKoH will be securely transferred from the data integration center at UMG to the independent evaluation team at Charité for the final analysis and provision of findings to the funding agency. Trained researchers of the evaluation team will code, enter and store the data on the secure Charité server. Only the evaluation team will have access to the final data set.

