### Statistical methods: sample size and power calculations.

The study includes 33 clusters in the region of West Pomerania, in which the participating university hospital is located. Sample size calculations were based on the Hussey & Hughes approach [22] for stepped-wedge cluster design for analysis with fixed time effects and random cluster effects.

The sample size calculation was based on the primary endpoint. As a basis for this calculation, we took the assumption that in the control group, the proportion of outpatient neurological symptoms that can be solved in the GP's practice (i.e., there is no subsequent neurological or special outpatient consultation or inpatient referral) is 0.2 (20%). We expect a 50% improvement (i.e., a 50% increase in effect size on the risk difference scale) in the intervention group, corresponding to an expected proportion of 0.3 (30%) in the intervention group.

With a total sample size of 1,089 participants (corresponding to 555 patients included in the control phase and 534 patients included in the intervention phase) at a type I error rate of 0.05, and an assumed coefficient of variation of 0.25, the study has a power of 80%, at a coefficient of variation of 0.20 and a power of 81% to measure the assumed effect size or a larger effect. Due to the nature of the intervention and the immediate collection of the primary endpoint data following the intervention, no attrition pertaining to this endpoint can be expected.

To achieve this number of cases, the stepped-wedge cluster randomized trial (CRT) must recruit, on average, at least 3 patients meeting the inclusion criteria, per cluster and step, to perform an appropriate analysis for this design.

To examine secondary endpoints (except those using claims data), all patients included during the study can be analyzed. Based on an estimate from experts of the NeTKoH study group, we assume an average demand of 6 to 8 neurological consultations per GP per month, which means about 3,168 neurological consultations per year in the whole region. Of these, about 25% of patients* (N = 792 per year, N = 66 per month) are insured by the participating statutory health insurances AOK Nordost and Techniker Krankenkasse. Assuming a loss of 30% due to non-participation or loss-to-follow-up, complete data of about 554 neurological consultations of the AOK Nordost and Techniker Krankenkasse patients per year and of about 1,269 to 1,690 patients during the whole study period are possible.

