### Health economic evaluation

The economic evaluation will be carried out alongside the trial. It will consist of a cost-utility analysis and three cost-effectiveness analyses. The outcome considered for the cost-utility analysis will be quality-adjusted life years (QALYs) derived from the EQ-5D-5L using German population weights [26]. Effectiveness measures will include the proportion of neurologic problems being solved at the GP’s office, the number of hospital stays, and the length of stay at the hospital. We will include all relevant additional trial costs of the intervention compared to standard care, as well as patient-specific costs stemming from claims data of the participating health insurances. The economic evaluation will be performed from a statutory health insurance perspective.

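### The number of hospital stays comes only from the 3-month patient interview, although claims for the same window are already obtained and could fill in and check part of the count

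*Protocol article*

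**What the plan says.** The Protocol article has two secondary outcomes on hospital use over the same window, from the initial GP appointment to the 3-month follow-up, and it takes them from different sources.

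- **Number of stays.** In the Participant timeline, the time-to-care endpoints, "as well as the number of hospital stays, will be assessed at" the 3-month follow-up, in both groups. The data are "taken in the form of a standardized telephone interview 3 months after the" initial GP appointment. The Table 1 row beginning "Number of hospital stays (for" lists the phone interview as the only instrument.
- **Hospital days.** Length of stay over that window "will be collected via claims data provided by the two participating health insurance providers". Table 1 lists claims data only.

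On coverage, the sample size section says of the expected consultations: "Of these, about 25% of patients" are insured with the two funds. It also says: "To examine secondary endpoints (except those using claims data), all patients included during the study can be analyzed".

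On loss, the data collection section says: "Since we are expecting attrition to occur, especially at the 3-months follow-up, reasons for dropouts and loss-to-follow-up will be collected". The sample size section allows for 30% dropout in the patient-reported secondary endpoints. Handling of missing values is left to the statistical analysis plan (SAP).

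**The concern.** Being interviewed at 3 months is not independent of what the interview asks about. A patient who is an inpatient when called, too ill to answer, or dead is less likely to supply a count, and these patients are more likely to have had a stay. The article names no proxy informant, practice or hospital record, or claims fallback for this outcome.

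The SAP can choose a method for missing values, but it works with the sources the protocol fixes. A mixed model fitted to interviewed patients does not recover stays that caused the non-response. For part of the sample, the trial already plans to hold data that could show those stays.

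The interview count is the only hospital outcome meant to cover patients of all insurers, and it is also an effectiveness measure in the health economic evaluation. As planned, the count describes interview responders from all funds, and the days describe patients of two funds. Nothing links the two.

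**Working it through.** **Inputs from the article:** 1,089 patients; 30% dropout for patient-reported secondary endpoints; about 25% insured with the two funds; 3,168 consultations per year.

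**The plan's own figures.** 0.25 × 3,168 = 792 insured consultations per year, and 0.70 × 792 = 554. Both match the article. The power for the patient-reported endpoints (310 vs 531, d = 0.20, two-sided 0.05) also reproduces, at 0.798 against the stated 0.80.

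**Patients without a count, and how many claims could reach**

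- No interview: 0.30 × 1,089 = 327.
- Insured with the two funds: 0.25 × 1,089 = 272.
- Insured and without an interview: 0.30 × 272 = 82.
- Beyond the reach of claims: 327 − 82 = 245, or 75% of the non-responders.

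The 82 is an upper figure. The 25% is an expert estimate for regional consultations, and the plan's 30% loss among insured patients includes non-participation.

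**Possible undercount in one group (assumed rates).** Let h be the true share with a stay, and let hospitalised patients be r times as likely as others to miss the interview. Overall loss is held at 30%. Loss among the others is q = 0.30 / (h·r + 1 − h), and the observed share is h(1 − r·q) / 0.70.

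| r | q at h = 10% | Observed share at h = 10% | Relative undercount, h = 5% to 15% |
|---|---|---|---|
| 1 | 0.300 | 10.0% | 0% |
| 1.5 | 0.286 | 8.2% | 17–20% |
| 2 | 0.273 | 6.5% | 32–39% |
| 3 | 0.250 | 3.6% | 56–74% |

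**Effect on the comparison (assumed rates).** Take true shares of 15% in control and 10% in intervention: difference 5.0 points, ratio 0.667. Hospitalised patients respond at rate s in both arms. Others respond at (0.70 − 0.10s)/0.90, which gives 70% overall in the intervention arm.

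| s | Control observed | Intervention observed | Difference (points) | Shrinkage | Ratio |
|---|---|---|---|---|---|
| 0.6 | 0.090/0.694 = 13.0% | 0.06/0.70 = 8.6% | 4.4 | 12% | 0.661 |
| 0.5 | 0.075/0.689 = 10.9% | 0.05/0.70 = 7.1% | 3.7 | 25% | 0.656 |
| 0.4 | 0.060/0.683 = 8.8% | 0.04/0.70 = 5.7% | 3.1 | 39% | 0.651 |

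**A milder mechanism (assumed).** Suppose the only extra loss is patients in hospital on the day of the call. With a 10-day stay in a 90-day window, that is 10/90 = 11% of those hospitalised, so their relative response is 0.889. Control is 0.15 × 0.889 / (0.15 × 0.889 + 0.85) = 13.6%. Intervention is 0.10 × 0.889 / (0.10 × 0.889 + 0.90) = 9.0%. The difference is 4.6 points, a shrinkage of about 9%.

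**Direction.** The shrinkage above assumes the same response pattern in both arms. If the true share were 10% in both arms, with r = 1 in one and r = 1.5 in the other, the first table gives 10.0% against 8.2%. That is a spurious 1.8 points whose sign depends on which arm has the higher r.

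**The case against.** The interview is a defensible choice. It gives one source, asked in the same way in both arms, for patients of every insurer. Claims cover only about a quarter. Replacing the interview with claims in that quarter would mix two measurement methods within the main analysis. This stands, and it is why the interview should remain the main source.

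Claims would also leave about 245 of 327 non-responders untouched. This stands too. The gain lies in a sensitivity analysis and in the first direct evidence on whether loss is related to hospitalisation.

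Most patients with a stay will be home again when called and can report it, and emergencies needing prompt inpatient care are excluded at entry. That argues for the milder calculation, although deaths and lasting illness would add to it by an unknown amount.

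A reader might infer more than the article supports:

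- *That the count is the only 3-month outcome bearing on harm.* Claims-based hospital days cover the same window without needing an interview, and EQ-5D-5L and its visual analogue scale are also taken at 3 months.
- *That dead or hospitalised patients are certain to be lost from the outcome.* No call-back rule is stated either way, reasons for loss are recorded, and missing-value rules are deferred to the SAP.
- *That the statement of no risk to patients rests on this interview.* The Discussion does not present it as a conclusion from interview data, and it adds that the trial is monitored and adverse issues reported.
- *That a new safety endpoint, or a rule for utilities after death, is missing.* The first would be an added endpoint. The second belongs to the SAP or the health economic plan, which are not shown.

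**Conclusion.** The point holds in a limited form. The article fixes the patient interview as the sole source for the number of hospital stays. It expects about 30% loss in patient-reported endpoints, and it assigns claims for the same window only to hospital days. Loss can depend on hospitalisation, serious illness or death, so the count may be too low.

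The size is not known. The relative undercounts of 17–74%, and the shrinkage in the absolute difference of about 9% to 39%, rest entirely on assumed hospitalisation and response rates. With equal response patterns in the two arms the ratio stays near its true value (0.65–0.66 against 0.667). With unequal patterns the bias could go either way. A reader might conclude that the trial will understate a benefit, but the documents do not support that.

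This concerns one of seven secondary outcomes and does not touch the primary outcome. It is worth correcting because data that would check and partly repair it are already planned.

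**What to change.** Keep the interview as the uniform source for all patients. In addition:

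1. Add claims data to the Table 1 row for the number of stays as a supplementary source, derived for **all** patients of the two insurers and not only for interview non-responders.
2. State a sensitivity analysis in which insured patients without an interview take their count from claims, with an indicator for the source.
3. Compare interview and claims counts in patients who have both. Compare claims-recorded hospitalisation between interview responders and non-responders, by arm.
4. Tabulate death and being in hospital at 3 months, from the reasons for loss already collected, by arm beside this outcome.

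The cost is wording in the protocol and SAP plus a modest amount of analysis. It assumes that the claims extract identifies separate stays, which should be confirmed with the insurers. The downsides are that claims cover only about a quarter of patients (at most about 82 of about 327 non-responders), and that the sensitivity analysis combines two sources that may not agree. The comparison in item 3 measures that disagreement.
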